## 2. Methods

### 2.1. Design and registration

This will be a pilot multicenter, open-label, prospective, randomized controlled clinical trial aiming to evaluate the efficacy and safety of *Baduanjin* in patients with moderate-to-severe COPD under remote monitoring and to explore the possible mechanisms involved in remission of the inflammation. After qualified recruitment, screening, and random assignment, a total of 150 participants from the Department of Respiratory Medicine of three teaching hospitals in Nanjing (China) will be included. All participants will be provided routine medication and lifestyle intervention, and they will be randomly assigned to one of three groups: a control group that will receive education on *Baduanjin* exercise, a classical PR group, and a *Baduanjin* group that will undergo a remotely monitored *Baduanjin* exercise program. The primary and secondary outcomes will be measured at baseline and at the cutoff point every 4 weeks. The exercise will be conducted at the outpatient clinic and monitored by a smartphone-based remote rehabilitation software program. The exercise program will last for 12 weeks, and the patients will be followed up for 24 weeks.

This work follows the Standard Protocol Items: Recommendations for Intervention Trials (SPIRIT).^[18]^ The flow chart of the participation screening process is shown in Figure 1, and the time points for enrollment, interventions, and assessments are shown in Figure 2. The study protocol has been registered with the Chinese Clinical Trial Registry (ChiCTR2100042700, http://www.chictr.org.cn/showproj.aspx?proj=120859).

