### 2.2. Sample size calculation

As documented previously, the primary outcome of the current study will be the 6-min walking distance (6MWD) at 12 weeks. According to a literature review, traditional Chinese exercise regimen was reported to be superior to the control intervention in the improvement of cardiopulmonary function when assessed using the 6MWD (580 ± 52.5 m in the *Tai Chi* group vs 564 ± 68 m in the control group, *P *= .035).^[19]^ In addition, significant improvement was observed in the PR group as compared to the control group (472 ± 62.56 m in the PR group vs. 355.49 ± 56.72 m in the control group, *P *< .001). We hypothesized that *Baduanjin* and PR would be superior to the control intervention in the improvement of cardiopulmonary function. Therefore, a sample of 40 to 43 patients (based on the estimation of data from Polkey et al^[19]^) could be assumed to have 80% power to detect significant differences between groups (*P* = .05, two-sided), with 20% inflation to account for dropouts. As a three-arm designed RCT, we adopted 50 patients per center (a final sample size of 150) to power the effect size of pre-specified interventions. The Power Analysis and Sample Size (PASS) software (v. 15.0.5; NCSS, LLC, Kaysville, UT) will be used in this study.

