### 2.6. Randomization

Statisticians who will not participate in the study will use the SPSS software (v. 24.0; IBM Corp., Chicago, IL) to generate random numbers, which will be placed in lightproof envelopes. Eligible participants will be assigned an envelope with group information.

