### 2.7. Interventions

All participants will be given routine medication and lifestyle intervention, and they will be randomly assigned to one of three groups: a control group, which will receive health education involving exercise methods, health regimens, and nutrition The participants will receive a health education brochure and will be followed up by phone call to discuss physical activity, disease progression, health status, and psychological status; a classical PR group, which will undergo PR training in the outpatient clinic, including power bicycle training, upper limb resistance training, and lower limb resistance training; and a *Baduanjin* group, which will perform *Baduanjin* exercise, displayed by video instructions on the participants’ smartphones installed with a remote rehabilitation software (Sukang R + health App, v. 5.1.40.0, Chengdu Shangyi Information Technology Co., Ltd., Chengdu, China) whilst wearing a heart rate belt (RecoveryPlus H1, Chengdu Shangyi Information Technology Co., Ltd.), which will be monitored remotely. Before the start of the experiment, professionals from Nanjing University of Traditional Chinese Medicine will teach the *Baduanjin* exercise (version from the General Administration of Sports) until the participants master the correct posture and stretching. Eight forms of *Baduanjin* Qigong exercise are shown in Figure 3. In both the PR and *Baduanjin* groups, the exercise intervention regimen will need to be performed for a cumulative time of 1 h per day, three times per week for 12 weeks.

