### 2.12. Statistical analysis

Statistical software (SPSS version 24.0, SPSS, IL) will be used for statistical analysis in this study. All data will be presented as descriptive row statistical analyses (mean ± standard deviation). For comparisons between the three groups, analysis of variance will be used in cases in which the normal distribution and homogeneity of variance assumptions have been verified; otherwise, the Wilcoxon rank sum test will be used. For intra-group comparisons, an independent sample *t* test will be used in cases in which the normal distribution and homogeneity of variance assumptions have been verified; otherwise, a paired sign rank sum test will be used. For baseline unequal data, the two groups will be compared by covariance analysis. Additionally, statistical data will be used to calculate the composition ratio and the rate of each indicator. The total effective rate will be compared between the groups using the c*hi*-squared test. Statistical significance will be set at *P* < .05.

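### The three-group ANOVA in 2.12 carries no hospital term although patients come from three hospitals; this costs a little precision, and adding hospital is nearly free

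*Protocol article*

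**What the plan says.** Section 2.12 states the between-arm comparison: "For comparisons between the three groups, analysis of variance will be used" when normality and equal variance have been verified, and a rank test otherwise. The only adjustment it offers is conditional and names neither hospital nor centre: "For baseline unequal data, the two groups will be compared by covariance analysis".

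The design is multicentre. Section 2.1 says that "a total of 150 participants from the Department of Respiratory Medicine of three teaching hospitals in Nanjing (China) will be included", and section 2.2 says "we adopted 50 patients per center (a final sample size of 150". Section 2.6 describes allocation by having statisticians use software "to generate random numbers, which will be placed in lightproof envelopes", and mentions no stratification or blocking by hospital. Section 2.7 has one arm treated on site, the PR group, "which will undergo PR training in the outpatient clinic". For sizing, section 2.2 says that "the primary outcome of the current study will be the 6-min walking distance (6MWD) at 12 weeks".

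**The concern.** Patients at one hospital may differ from those at another, and the walk test may be run differently. Section 2.14 shows that one of the three is a geriatric hospital, and section 2.4 admits ages 40 to 75, so some difference in case mix is plausible. Hospital is known for every patient at no cost. An analysis that leaves it out keeps between-hospital variation in the error term. How much that matters depends on the allocation:

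- **Not stratified by hospital:** the arms can end up with different hospital mixes by chance, which adds noise to the arm difference.
- **Balanced within hospital:** the arm difference is already protected, but the ANOVA does not know it and reports standard errors that are too large.

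What is at stake is efficiency, and how easily one realised result can be read. The validity of the test is not in question.

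**Working it through.** The plan gives no figure for hospital variation, so there is none to reproduce. The check asks what omitting hospital costs over a stated range.

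**1. Inputs**
- SDs of 52.5 m and 68 m (section 2.2). Pooled variance = (52.5² + 68²)/2 = 3690, so the SD is 60.7 m, taken as the residual SD.
- Three hospitals with 50 patients each and 20% dropout (section 2.2): 50 × 0.8 = 40 evaluable per hospital, 120 in all.
- Between-hospital SD: **assumed**, at 10, 15, 20 or 25 m.

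**2. Validity under unstratified allocation**
- With 50 per arm and 50 per hospital, the number from one hospital in a given arm averages 50/3 = 16.7. Its 95% range is 11 to 22 (hypergeometric: 150 patients, 50 at the hospital, 50 in the arm).
- In simulations of 3,000 trials per setting, with hospital at 0 to 20% of the variance, the ANOVA without hospital rejected a true null in 4.6% to 5.2% of trials. The mean estimated difference under the null was within about 0.1 m of zero.
- Chance imbalance is therefore already reflected in the standard error.

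**3. Precision under unstratified allocation**

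Simulated trials had 3 × 40 patients and simple randomisation, with hospital effects drawn afresh in each trial. The table gives the SD of the Baduanjin-minus-control difference without hospital divided by the SD with hospital, and the sample equivalent (ratio² − 1).

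| Assumed hospital SD | SD ratio | Sample equivalent |
|---|---|---|
| 10 m | 1.001 | 0.2% |
| 15 m | 1.013 | 2.6% |
| 20 m | 1.026 | 5.3% |
| 25 m | 1.049 | 10.0% |

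At 25 m the SDs are 14.5 m without hospital and 13.8 m with it. The extra noise is about √(14.5² − 13.8²) = √19.8 ≈ 4.5 m, against the 16 m difference (580 − 564) quoted in section 2.2.

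**4. Cross-check by formula**
- With three hospitals, the expected variance among the hospitals actually in the trial is two thirds of the assumed value s². The ratio is then about √(1 + (2/3)s²/3690) = 1.009, 1.020, 1.036 and 1.055.
- The simulated ratios are lower by 0.6% to 1.0%: 1.009/1.001 = 1.008, 1.020/1.013 = 1.007, 1.036/1.026 = 1.010, 1.055/1.049 = 1.006. This is roughly what estimating two more terms under uneven allocation costs.

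**5. If allocation is balanced within hospital**
- Type I error of the ANOVA without hospital falls to 0.043, 0.034 and 0.024 when hospital makes up 5%, 10% and 20% of the variance (50 per arm, 3,000 trials each). With hospital in the model it stays at about 0.05.
- On the scale of step 4, an assumed SD of 25 m gives a share of 417/(417 + 3690) = 10%, where 417 = (2/3) × 625. The 20% figure therefore lies outside the assumed range.

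**The case against.** The strongest reply is that this is an omission in a condensed article. Section 2.12 says analysis of variance, not one-way analysis of variance. Nothing in it forbids a centre factor, and an analysis plan that is not shown could contain one. That stands as a caution. But the section does more than defer: it names the test, its assumption checks, its fallback and its one adjustment, and hospital appears in none of them.

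Other points also stand:

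- **Size.** Everything rests on an assumed between-hospital SD. The hospitals are in one city, and the Discussion itself calls this a single geographical area, so the upper part of the range may be too high. At 10 m the gain is essentially nil.
- **Fifty per centre.** The phrase follows a reference to the three-arm design, and 40/0.8 = 50, so it may be a slip for 50 per group. The equal split between hospitals is then not secure, but three hospitals contribute either way.
- **Covariance analysis.** It could absorb some case-mix difference, but only where baseline values are judged unequal.

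Three stronger readings are tempting and not supported:

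- A reader might infer that hospital differences bias the Baduanjin effect or inflate false positives. Step 2 of the working shows neither.
- A reader might use √(1 + s²/3690) and conclude that 3% to 17% of the sample is lost. That formula ignores that only three hospitals are sampled and that the extra terms have a cost.
- A reader might expect a hospital term to remove differences in how PR is delivered. Those are treatment-by-hospital differences, and a main effect does not remove them.

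**Conclusion.** The point holds as a modest efficiency improvement. The stated test does not use a design feature that is known for every patient. It remains valid on average under unstratified allocation, and becomes conservative if allocation is balanced within hospital. For assumed between-hospital SDs of 10 to 25 m and a residual SD of 60.7 m, omitting hospital makes the SD of the arm difference about 0% to 5% larger, equivalent to about 0% to 10% of the sample. The documents show no systematic bias. The change is worth making because it is nearly free, and it should be settled before outcome data are seen.

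**What to change.** In section 2.12, analyse 6MWD, SGRQ and the continuous secondary outcomes with a linear model containing treatment and hospital as fixed factors. Report the arm differences and their confidence intervals from that model, and show results by hospital descriptively. In section 2.6, state whether allocation is stratified by hospital, since that decides which of the two situations applies.

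The cost is one added term, two degrees of freedom and no new data. If hospitals do not differ, the loss of precision is under 1%. The sample size need not change. Differences between hospitals in PR delivery are not addressed by this change; the by-hospital display would only describe them.

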### 2.8. Efficacy assessments

The effects of *Baduanjin* exercise, including clinical symptoms, quality of life, activity and endurance, lung function, and respiratory muscle function, will be evaluated in patients with moderate-to-severe COPD and compared with the effects of the control and PR interventions. The primary outcomes will include the 6MWD and the St. George’s Respiratory Questionnaire index. The secondary outcomes will include lung function test results, including FEV_1_, forced volume capacity (FVC), ratio of FEV_1_ to FVC (FEV_1_/FVC%), maximum expiratory flow rate, and maximum ventilation per minute; chest high-resolution computed tomography to compare the cross-sectional area of the pectoralis major and subcutaneous fat; Modified Medical Research Council scale; COPD assessment test questionnaire results; lower extremity muscle strength; and Short-Form 36-item Health Survey for healthy living results.

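### The between-group test for 6MWD and SGRQ is chosen by assumption checks on the data, and the fallback is a two-sample rank test that does not remedy unequal variances or test the means being reported

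*Protocol article*

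**What the plan says.** Section 2.12 opens its between-group rule with "For comparisons between the three groups". It then makes the method conditional, permitting analysis of variance only "in cases in which the normal distribution and homogeneity of variance assumptions have been verified; otherwise, the Wilcoxon rank sum test will be used". Both conditions must be met for analysis of variance, so failure of either one, including unequal variance alone, leads to the rank test. The section names no check and no threshold, and it gives no separate analysis for the primary outcomes. It also says that all data will be shown as mean and standard deviation, without regard to the test used.

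On what is primary, section 2.2 states that "the primary outcome of the current study will be the 6-min walking distance (6MWD) at 12 weeks", and section 2.8 states that "The primary outcomes will include the 6MWD and the St. George’s Respiratory Questionnaire index". Section 2.2 sets out its planning figures as mean 6MWD with SD, for example "564 ± 68 m in the control group" against 580 ± 52.5 m in the Tai Chi arm. The SDs it quotes are not equal.

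**The concern.** There are three difficulties, and all lie in what the rule states.

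1. **Wrong remedy.** Read as a test of location, a rank test also needs similar spread in the arms. With unequal spread it is not a test of equal means or of equal medians. If variance is the problem, a Welch or robust-variance analysis deals with it and keeps the comparison of means.
2. **Wrong number of groups.** The Wilcoxon rank sum test compares two samples, but the sentence is about three groups. Once the fallback is triggered, the analyst has to decide something the rule does not settle: a Kruskal-Wallis test, or a set of pairwise tests.
3. **A changed target.** In the analysis-of-variance branch the P value concerns the mean difference in metres. In the rank branch it does not, yet the means and SDs will still be displayed beside it.

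At stake is whether the primary result answers one question fixed in advance. As written, the test and the quantity it addresses depend on how the diagnostics fall.

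**Working it through.** **The plan's own figure.** Section 2.2 gives 40 to 43 patients for 80% power. With a difference of 580 − 564 = 16 m and a pooled SD of √[(52.5² + 68²)/2] = 60.75 m, the usual two-sample calculation (two-sided .05) gives 227 per arm, so 40 to 43 is not reproduced. That is a separate matter. It is used here only to choose arm sizes: 40 evaluable, and 40/(1 − 0.20) = 50 before dropout. Fifty per arm also follows from 150 in total if allocation is equal.

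**Inputs.** SDs of 52.5, 68 and 62.56 m come from section 2.2. They are drawn from two different comparisons, so they illustrate plausible inequality and are not a stated assumption for this trial's arms. Assumed: normal data, equal means, Shapiro-Wilk in each arm plus one Levene test, each at .05, and Kruskal-Wallis standing in for the three-group rank test.

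**Step 1: switching when every assumption holds.** Three normality checks and one variance check, treated as independent, give

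1 − 0.95⁴ = 1 − 0.8145 = 18.5%.

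Simulation at 40 per arm gives 18.4% (6,000 trials) and 19.4% (2,000 trials), so about 19%.

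**Step 2: switching with SDs like those in section 2.2.**

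| Arm size | Levene alone significant | Either check triggers the rank test |
|---|---|---|
| 40 per arm | about 25% | about 34% (separate runs: 33.1% to 37.0%) |
| 50 per arm | about 30% | about 39% |

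The spread between runs reflects Monte Carlo error (about 1 percentage point at 2,000 trials) and whether Levene is centred on the mean or the median. Variance, more than normality, now drives the switch, and variance is the condition for which the rank test is the wrong remedy. Under one assumed left-skewed distribution the switch occurs in about 96% of trials.

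**Step 3: false-positive rate of the whole two-stage rule.**

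| Case (2,000 trials each) | Two-stage rule | ANOVA alone | Rank test alone |
|---|---|---|---|
| Equal SDs, 40 per arm | 5.2% | 5.0% | 4.7% |
| Section 2.2 SDs, 40 per arm | 5.3% | 5.1% | 5.6% |
| Section 2.2 SDs, 50 per arm | 5.3% | 5.3% | 4.8% |
| Section 2.2 SDs, skewed, 40 per arm | 6.2% | 5.2% | 6.2% |
| Section 2.2 SDs, arms of 30/40/50, largest SD in smallest arm | 6.3% | 6.2% | 6.5% |

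The Monte Carlo standard error is about 0.5 percentage points. Error rates barely move with equal arms. In the last row, where unequal variance does matter, the rank test is no closer to 5% than analysis of variance, so the switch brings no protection there.

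**Step 4: the quantity tested.** Setting sections 2.2 and 2.12 side by side, planning is in mean metres and presentation is in mean and SD. Only one of the two possible tests addresses a difference in means.

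**The case against.** The strongest reply is that little is lost. The rule is written down before the data, choosing a test by assumption checks is a common convention, and type I error stays near nominal. Where it rises to about 6% with unequal arms, analysis of variance alone does the same. The named checks and thresholds are detail that an article may leave to an analysis plan that is not shown. The switching rates rest on assumed checks, and visual or residual-based checking would give others. All of this stands, and it limits the size of the point. It does not rescue the rule itself: sending unequal variance to a rank test, and naming a two-sample test for three groups, are positive statements and not omissions.

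A reader might go further in three ways that the document does not support.

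- **That the result would be lost to later meta-analysis or could not be set against the planned difference.** Section 2.12 promises mean and SD for all data, so a mean difference and an unadjusted interval can be computed whichever test is run.
- **That tests differing from visit to visit undermine the primary result.** Outcomes are measured every 4 weeks, but section 2.2 ties primary 6MWD to week 12 alone. Any rate of mixed methods over visits also depends on the correlation between repeated measurements in the same patients, which the document does not give.
- **That the switch costs the trial its covariate adjustment.** The analysis-of-variance branch is equally unadjusted. Baseline imbalance has its own sentence: "For baseline unequal data, the two groups will be compared by covariance analysis".

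**Conclusion.** The point holds as a flaw in a stated rule. Section 2.12 leaves the primary test, and with it the quantity tested, to the outcome of unnamed checks, and its fallback is unsuited both to unequal variances and to three groups. Under the assumed checks and normal data, the chance of landing in the fallback runs from about one in five with equal SDs to between one in three and two in five with SDs like those in section 2.2. Those rates are illustrative. The conclusion does not depend on their exact values, only on the switch being a real possibility.

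The evidence does not show a materially inflated false-positive rate. The consequence is one of interpretation: a primary P value that may not refer to the means shown with it. It should be corrected, but it does not threaten the trial's validity.

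**What to change.** In section 2.12, replace the conditional rule for the primary outcomes with one analysis fixed in advance. For week-12 6MWD, and likewise for SGRQ, use a linear model with heteroscedasticity-robust standard errors, or a Welch-type comparison of means. Apply it whatever the diagnostics show, and report pairwise mean differences with 95% confidence intervals. Keep rank methods as a labelled sensitivity analysis, or as the named method for the ordinal mMRC score, with Kruskal-Wallis for three groups and the rank sum test for pairs.

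The cost is a few sentences of text. No change to data collection or sample size is involved. The one statistical downside is slightly lower efficiency than a rank test if 6MWD proves heavily skewed, and the sensitivity analysis would make that visible.

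### Two tests named in the statistical analysis section do not fit the data: an independent-samples t test for within-group change, and a two-sample rank sum test as the three-group fallback

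*Protocol article*

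**What the plan says.** Section 2.12 of the protocol article gives a parametric test and a fallback for each type of comparison.

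- Between groups: "For comparisons between the three groups, analysis of variance will be used" if normality and equal variance have been verified; "otherwise, the Wilcoxon rank sum test will be used".
- Within groups: "For intra-group comparisons, an independent sample *t* test will be used" under the same two conditions; "otherwise, a paired sign rank sum test will be used".

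The section closes with a single threshold: "Statistical significance will be set at *P* < .05".

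Section 2.1 supplies the design facts that decide whether these tests fit. On arms, "they will be randomly assigned to one of three groups". On timing, "The primary and secondary outcomes will be measured at baseline and at the cutoff point every 4 weeks". Nothing elsewhere in the article changes either choice of test.

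**The concern.** A within-group comparison in this design sets a patient's later value against the same patient's baseline. The independent-samples t test treats the two sets of values as coming from unrelated people and so ignores their correlation. The paired fallback shows that the authors had matched data in mind. As written, the same data are treated as unmatched when they look normal and as matched when they do not. The equal-variance condition is also out of place, since it belongs to the two-sample t test and not to the paired one.

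The rank sum test compares two samples and has no three-group form. When the assumptions of the analysis of variance fail, the plan names no test that answers its own three-group question. The analyst would have to choose one at that stage, and if the choice were unadjusted pairwise testing, the error rate over the three comparisons would exceed .05.

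**Working it through.** The article states no figure that depends on these choices, so there is none to reproduce. The check is of how the named tests behave.

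**Inputs**

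- SD of 6-minute walking distance, from the Tai Chi and control SDs in section 2.2: sqrt((52.5² + 68²)/2) = 60.7 m.
- n = 40 for one group, the lower end of the range in section 2.2.
- Before-after correlation r: not in the article; assumed 0.5 to 0.8.
- Within-group change of 25 m: not in the article; assumed for illustration.
- 50 per arm for the three-group check: 150 patients in three arms, assuming equal allocation (section 2.2 speaks of 50 per center).

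**1. Independent t test on before-after data**

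True SE of the mean change: SD × sqrt(2(1-r)/n). SE used by the independent test: SD × sqrt(2/n). Ratio: 1/sqrt(1-r). Approximate true two-sided size at a nominal .05: 2Φ(-1.96/sqrt(1-r)).

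At r = 0.7:

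- Independent SE = 60.7 × sqrt(2/40) = 13.6 m.
- Paired SE = 60.7 × sqrt(0.6/40) = 7.4 m.
- The independent test (78 df, critical value 1.99) needs an observed change of about 27.0 m. The chance of reaching it when the true change is 25 m is Φ((25 - 27.0)/7.43) = 39%.
- The paired t test has a standardized change of 25/7.43 = 3.36, which gives power of 91% on 39 df.

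| Assumed r | SE ratio | True size | Power, independent | Power, paired |
|---|---|---|---|---|
| 0.5 | 1.41 | .0056 | 42% | 72% |
| 0.7 | 1.83 | .00035 | 39% | 91% |
| 0.8 | 2.24 | .00001 | 37% | 98% |

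A simulation with 20,000 runs at n = 40 agrees. The independent test rejected a true null in .007, .0004 and none of the runs at r = 0.5, 0.7 and 0.8; the paired test rejected in .048 to .051.

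The power loss depends on the change assumed. Using 16 m, the Tai Chi versus control difference in section 2.2, as a within-group change with n = 50, simulated power (independent versus paired) is .22 versus .34 at r = 0.3, .18 versus .44 at r = 0.5 and .12 versus .65 at r = 0.7.

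**2. Rank sum test with three arms**

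Three arms give three pairs. Simulation under no difference (10,000 runs, 50 per arm, lognormal data):

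- At least one of three unadjusted pairwise rank sum tests below .05: 11.8%. Three independent tests would give 1 - 0.95³ = 14.3%; pairs that share an arm are correlated, so the true figure is lower.
- Kruskal-Wallis across the three arms: 4.8%.
- Pairwise rank sum tests read only after a significant Kruskal-Wallis test: 4.8% under the global null.

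**The case against.** The strongest case on the other side is that the trial's question lies between arms. Section 2.2 powers differences between groups, and section 2.12 answers with analysis of variance, or covariance analysis for unequal baselines. The t-test slip touches neither. Within-group change is not a randomized comparison, and the error there is conservative. All of this stands, and it limits how serious the point is.

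A second argument is that this is only loose wording: paired may have been meant in one place and Kruskal-Wallis in the other, and an unshown analysis plan may say so. That is possible, and the misplaced equal-variance condition fits a drafting slip. It does not remove the point, because the article does not leave the tests open. It names them, and the names are wrong or contradictory as they stand.

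A reader might go further than the documents allow in four ways:

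- That false positives are inflated within groups. With positive correlation the reverse is true.
- That the between-arm result is invalid. The analysis of variance is untouched where its assumptions hold.
- That the trial runs at 12% error. The article does not say that rank sum tests will be run pairwise, or that they would go uncorrected. If Kruskal-Wallis is what is meant, there is no inflation.
- That reported intervals will be wrong. Section 2.12 promises means, SDs and P values, not confidence intervals.

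**Conclusion.** The point holds as a correction to two named tests, not as a threat to the main comparison.

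The mismatch itself follows from the text and needs no assumption. Its size does. The loss of within-group sensitivity rests on a positive before-after correlation that the article does not give, and the 39% versus 91% contrast is one scenario that also rests on the assumed 25 m change. The family error of about 12% is conditional on uncorrected pairwise use.

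Only the rank sum part can reach a randomized comparison, and only for outcomes where normality or equal variance fails. That could include either primary outcome. The article also has measures for which the fallback may well be needed, such as the graded dyspnea scale in section 2.8 and the cytokines in section 2.10.

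**What to change.** In section 2.12, or in the analysis plan before the data are analysed:

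- Within groups: name a paired t test, with the Wilcoxon signed rank test as fallback. Judge normality on the before-after differences and drop the equal-variance condition. Label these results descriptive.
- Between groups: name Kruskal-Wallis as the fallback to analysis of variance. Keep the rank sum test only for pre-specified pairwise contrasts, and state the multiplicity adjustment.

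This changes test names and a sentence or two. It needs no extra patients, visits or data.

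### Baseline adjustment depends on an undefined baseline imbalance and is worded for two arms of three, which gives up precision and leaves chance imbalance in the estimate

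*Protocol article*

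**What the plan says.** Section 2.12 (Statistical analysis) sets the default: "For comparisons between the three groups, analysis of variance will be used", provided that normality and equal variance have been verified, and a rank test otherwise. Neither uses the baseline value. Baseline enters through one later sentence: "For baseline unequal data, the two groups will be compared by covariance analysis". The section does not say what counts as unequal, which variable is the covariate, or which two groups are meant. It also does not say whether week-12 values or changes from baseline are analysed.

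Section 2.1 (Design and registration) describes three arms ("they will be randomly assigned to one of three groups") and states: "The primary and secondary outcomes will be measured at baseline and at the cutoff point every 4 weeks". Section 2.8 (Efficacy assessments) names two continuous primary outcomes: "The primary outcomes will include the 6MWD and the St. George’s Respiratory Questionnaire index". No other section provides for routine baseline adjustment.

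**The concern.** In a randomised trial any baseline difference between arms is due to chance. The reason to adjust is that baseline predicts outcome, and comparing the arms at baseline does not measure that. A rule that waits for visible imbalance therefore has three costs:

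- In most trials it never switches on, so the precision available from baseline is lost.
- An imbalance too small to trigger it stays in the estimate.
- Because the trigger is undefined, the model can be chosen after the data are seen. The trial is open-label, and section 2.11 gives randomisation and analysis to the same statistician, so a fixed rule is worth more here than usual.

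The reference to two groups adds an ambiguity: it does not say how covariance analysis would apply to three arms.

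**Working it through.** **Inputs from section 2.2 (Sample size calculation).** The effect comes from "580 ± 52.5 m in the *Tai Chi* group vs 564 ± 68 m in the control group", with the ± figures read as standard deviations. The difference is 580 − 564 = 16 m. The pooled SD is √((52.5² + 68²)/2) = √3690.1 = 60.75 m. The test is two-sided at 0.05 with 80% power, and dropout is 20%.

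**Assumptions.** Equal allocation gives 50 per arm, because the text says 50 per centre and 150 in total. Completers are then 50 × 0.8 = 40 per arm. The correlation r between baseline and week-12 6MWD is not in the article, so 0.5, 0.7 and 0.8 are shown. SD is taken as equal at baseline and week 12.

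**The plan's own figure.** The article arrives at 40 to 43 patients for 80% power. From its 16 m and 60.75 m, n per arm = 2 × (1.96 + 0.842)² × 60.75² / 16² ≈ 226.3, so 227. The rehabilitation data ("472 ± 62.56 m in the PR group vs. 355.49 ± 56.72 m in the control group", a difference of 116.51 m) need about 5 per arm. Neither source gives 40 to 43; only the dropout step 40/0.8 = 50 reproduces. That is a separate matter. It bears on this point only because a trial with little power for 16 m can least afford to lose precision.

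**Gain from adjusting in every case.** The residual SD is SD × √(1 − r²) for covariance analysis and SD × √(2(1 − r)) for change scores. Results are for 40 per arm by the two-sample t calculation:

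| Analysis | r | SD used (m) | Detectable difference (m) | Power for 16 m |
|---|---|---|---|---|
| Week-12 value, unadjusted | any | 60.75 | 38.5 | 21% |
| Covariance analysis | 0.5 | 52.6 | 33.4 | 27% |
| Covariance analysis | 0.7 | 43.4 | 27.5 | 37% |
| Covariance analysis | 0.8 | 36.4 | 23.1 | 49% |

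With change scores at r = 0.7 the SD is 60.75 × √0.6 = 47.1 m and power is 32%, against 37% with covariance analysis. At r = 0.5 the change-score SD is again 60.75 m, so power is 21% against 27%.

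**What the conditional rule recovers.** The rule was simulated for a two-arm comparison of week-12 values at 50 per arm, reading unequal as a baseline p<0.05 (40,000 runs per setting). Covariance analysis is then triggered in about 5% of trials.

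| r | Power for 16 m, conditional rule | Power for 16 m, always adjusted | Type I error, conditional rule |
|---|---|---|---|
| 0.5 | 25.6% | 32.4% | 4.6% |
| 0.7 | 25.3% | 44.1% | 3.4% |
| 0.8 | 26.0% | 58.1% | 3.0% |

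Almost none of the gain is recovered, and the rule is conservative overall.

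**Imbalance left in the estimate.** At 40 per arm the standard error of a baseline difference is 60.75 × √(2/40) = 13.58 m. A difference of up to 1.96 × 13.58 = 26.6 m would pass as not unequal at p<0.05. An analysis of week-12 values carries r times that difference into the result: 13.3, 18.6 and 21.3 m for r = 0.5, 0.7 and 0.8. These are upper limits, not typical values, but they are of the same order as the 16 m effect cited. With change scores the carry-over is (1 − r) times the difference in the opposite direction, which is 0.3 × 26.6 = 8.0 m at r = 0.7.

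**The case against.** **The article is a condensed document.** Detail on covariates is commonly left to a statistical analysis plan. That would answer a complaint that adjustment is missing, but the article states a rule, and the rule is the problem.

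**A reader might infer an excess of false positives.** If only trials with a baseline difference of 1 to 1.96 standard errors are considered (about 27% of trials at r = 0.7 and 40 per arm), type I error is about 8.4% and the carry-over averages about 13 m. This selects the unfavourable band. In trials with a difference below 1 standard error, about two thirds, the rate is about 1.5%, and over all trials it is below 5%. Nor is the 13 m a bias in the usual sense: its sign follows the direction of the imbalance, and it averages to about zero over randomisations. The band also depends on a p<0.05 trigger that the article does not state.

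**A reader might infer that adjustment is worth doubling the sample.** At r = 0.7, 1/(1 − 0.49) = 1.96, but only against unadjusted week-12 values. Section 2.12 does not say which form is analysed, and section 2.2 speaks of improvement. Against change scores at r = 0.7 the variance ratio is 0.60/0.51 = 1.18. The article therefore does not fix the size of the gain.

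**Centre.** Section 2.6 (Randomization) describes no stratification by centre, and no figure in the article supports a gain from a centre term. Its absence is not a fault.

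**Two groups.** This may be loose wording for pairwise comparisons, since the default sentence refers to three groups correctly. It still needs clarifying.

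What stands against the plan is an undefined, data-dependent rule that discards baseline information in most trials.

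**Conclusion.** The concern holds as a matter of precision and prespecification, not of false-positive control. The direction is certain: for any correlation clearly above zero, routine covariance analysis is more precise than unadjusted week-12 values, and it is at least as precise as change scores. The size is conditional on the assumptions listed: 40 completers per arm, SD 60.75 m, and r between 0.5 and 0.8. Under them the detectable difference falls by about 5 m (38.5 − 33.4) to 15 m (38.5 − 23.1) if week-12 values are analysed, and the gain is smaller if changes are. All figures concern 6MWD. The article gives no SD or effect for SGRQ, so only the general variance factor 1 − r² can be stated for that outcome. This should be corrected before analysis; it does not make the trial invalid.

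**What to change.** In section 2.12, prespecify the primary analysis of 6MWD and SGRQ as a covariance analysis of the week-12 value, with arm as a three-level factor and the baseline value of the same outcome as covariate. Apply it whatever the observed baseline balance, and take the pairwise arm comparisons from that model. For these two outcomes, delete the condition on unequal baseline data and the reference to two groups. A mixed model over the 4-weekly visits with the same terms and a week-12 contrast is an acceptable alternative, and a centre term is optional.

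The cost is a sentence or two. The baseline values are already scheduled for collection, the stated software (SPSS 24) fits the model, and no change to recruitment or visits is needed.
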